### Sample size

The sample size calculation was conducted using the G Power program with an alpha of 5% and beta of 80%, and thus we obtained the sample size of 15 volunteers in each group.

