### Exclusion criteria

Volunteers will be excluded who present with unstable heart conditions, fibromyalgia, deambulation disability, knee or hip arthroplasty, and contraindications for aquatic physiotherapy [13]. Also excluded will be those who miss two consecutive sessions without justification, as well as volunteers who are absent from 10% of the intervention sessions and who change their dose or class of medication.

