### Randomization and allocation

The randomization method used will be a simple draw conducted by a research employee. Volunteers will then be divided into two groups: an aquatic intervention group (WG; *n* = 15) and a control group (CG; *n* = 15) [17]. CG volunteers will not perform any type of exercise or physical therapy.

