### Analysis

The normality of the data will be verified with the Shapiro-Wilk test. Parametric data will expressed as mean and SD, using Student’s *t* test for independent samples to compare the groups and two paired samples to compare the times. For the analysis of repeated measures, analysis of variance with a post hoc Tukey test will be used. Nonparametric data will be expressed as median, maximum, and minimum values. The Mann-Whitney *U* test will be used to compare the groups, and for comparison of moments, the Wilcoxon test will be applied. In all tests, results will be judged to be statistically significant when α values are <0.05.

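### The sample size section prints beta as 80%, which is 20% power; 80% power was almost certainly meant, and 15 per group cannot follow from alpha and beta alone

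*Protocol article*

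**What the plan says.** The Sample size section is one sentence. It names the software ("The sample size calculation was conducted using the G Power program") and then reports the result: "with an alpha of 5% and beta of 80%, and thus we obtained the sample size of 15 volunteers in each group". It gives no effect size, standard deviation, outcome, test, sidedness or allowance for losses. No outcome is called primary anywhere in the article text.

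Three other sections bear on the figure:

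- **Randomization and allocation** assigns 15 volunteers to the aquatic group and 15 to the control group, the same number that the calculation produced.
- **Exclusion criteria** also removes people who miss two consecutive sessions without justification, and "volunteers who are absent from 10% of the intervention sessions" together with a medication-change condition.
- **Analysis** uses Student's t "test for independent samples to compare the groups", with paired tests over time, repeated-measures analysis of variance and nonparametric alternatives. Its threshold is that "results will be judged to be statistically significant when α values are <0.05". It does not say whether tests are one- or two-sided.

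**The concern.** Beta is the probability of missing a real effect, and power is 1 − beta. A beta of 80% therefore describes a trial that would miss its target effect four times in five. This is the only sentence in the article on what the trial can detect, and its key figure is wrong as it stands.

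The inference is also incomplete. Alpha and beta fix a group size only once an effect size and a test are added, so a reader cannot tell what difference 15 per group was meant to detect.

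What is at stake is how the results are read. The Discussion expects benefit in the aquatic group and no change in controls. With groups this small, a non-significant comparison is quite compatible with a moderate benefit, and the article gives a reader no means of seeing that.

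**Working it through.** **Inputs from the article.** Alpha 0.05; 15 per arm, both calculated and allocated; independent-samples t test between groups; 12 weeks × 3 sessions = 36 sessions.

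**Assumptions.** Two-sided testing (one-sided also shown), a single post-treatment measurement, and the loss scenarios in step 5.

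**1. Stated power.** Power = 1 − beta = 1 − 0.80 = 0.20.

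**2. Reproducing 15 per group.** This cannot be done. The calculation needs a standardised difference d, and none is given. The check is therefore run backwards, from 15 per arm to d.

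**3. Detectable difference.** The t statistic has n1 + n2 − 2 = 28 degrees of freedom and noncentrality d × √(n1·n2/(n1 + n2)) = d × √(225/30) = 2.739d. The two-sided critical value is 2.048. Solving the noncentral t distribution for d:

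| Reading | Two-sided | One-sided |
|---|---|---|
| Power 80% (beta 20%) | 1.06 SD | 0.93 SD |
| Power 20% (beta 80%, as printed) | 0.42 SD | 0.30 SD |

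Normal-approximation check at 80% power, two-sided: (1.960 + 0.842) × √(2/15) = 1.02 SD, close to the exact value.

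The 1.06 SD depends on the design. If baseline is adjusted for, it is multiplied by √(1 − r²). At assumed correlations of 0.5 and 0.7 this gives 1.06 × √0.75 = 0.92 SD and 1.06 × √0.51 = 0.76 SD. For a comparison of change scores the factor is √(2(1 − r)). At 0.5 it stays at 1.06 SD, and at 0.7 it is 1.06 × √0.6 = 0.82 SD.

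**4. Power with 15 v 15, two-sided t test.** It is 26% at 0.5 SD, 56% at 0.8 SD and 75% at 1.0 SD. The 95% confidence interval for the difference has half-width 2.048 × √(2/15) = 0.75 SD.

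**5. Losses after allocation.** Ten percent of 36 sessions is 3.6 sessions. Attendance can be judged only after allocation, and controls have no sessions to miss. The article gives no loss rate, so the following is an assumed range. It shows power at 1.06 SD, the difference that gives 80% with 15 v 15:

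| Analysed | Power at 1.06 SD |
|---|---|
| 15 v 15 | 80% |
| 12 v 15 | 75% |
| 12 v 12 | 70% |
| 10 v 10 | 61% |

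The symmetric rows are included because the medication-change condition could apply in either arm.

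**The case against.** The strongest reply is that one word is wrong and nothing else. Eighty percent is the conventional value for power, G*Power cannot return a sample size without an effect size, and a journal article may leave that input to a fuller document. Correcting the word alters neither enrolment nor conduct.

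Much of this stands, and it rules out several stronger readings:

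- **That the trial was designed for 20% power.** That is what the sentence literally says, but it is not a plausible design intention.
- **That 15 per group is a miscalculation.** The article does not show the inputs, so this cannot be established.
- **That the trial can detect nothing below 1.06 SD.** That figure belongs to a two-sided t test on one measurement. The Analysis section also plans paired and repeated-measures analyses and does not say which was entered in G*Power.
- **That fewer than 15 per arm will be analysed.** The article does not say how many will be excluded, whether they will be replaced, or whether the 15 is counted before or after exclusion.

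The reply does not rescue the printed beta. That is a misstatement rather than an omission, so condensation does not explain it. Nor does it remove the fact that the calculated and allocated numbers coincide while some exclusions operate after allocation.

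**Conclusion.** The concern holds in limited form. The stated power is wrong as written, almost certainly a slip for 80%, and the group size does not follow from the two quantities given.

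Read as 80% power, 15 per arm corresponds to about 1.06 SD two-sided, or 0.93 SD one-sided, for the independent t test. A baseline-adjusted or repeated-measures comparison with high correlation could detect less than that. Under the two-sided t test, effects of 0.5 and 0.8 SD would be found with only 26% and 56% power. These figures measure sensitivity and should not be taken as the effect the trial was designed around.

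The point about losses survives in a smaller form: no allowance is visible, and the size of any shortfall is unknown.

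Low power also does not mean that a null result excludes nothing. With a half-width of about 0.75 SD, an estimate near zero would still rule out differences beyond roughly that size. The confidence interval, and not the power figure, should carry the interpretation.

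**What to change.** 1. Replace the beta figure with power 80% (beta 20%) and alpha 5%. State the sidedness, test, outcome and effect size actually entered in G*Power.
2. If that input cannot be recovered, say so. Then report the detectable difference as a sensitivity statement, not as the design effect: *with 15 v 15 analysed and an independent t test, 80% power requires about 1.06 SD two-sided (0.93 SD one-sided); two-sided power is 26% at 0.5 SD and 56% at 0.8 SD*. Note that the detectable difference is smaller if the comparison is baseline-adjusted or uses repeated measures at high correlation.
3. State that the power applies only if all 15 per arm are analysed. Give power over a range of losses labelled as assumed, for example 75% at 12 v 15, 70% at 12 v 12 and 61% at 10 v 10, all at 1.06 SD.
4. Add that a non-significant result will be interpreted from its 95% confidence interval (half-width about 0.75 SD with 15 v 15), not as evidence of no effect.

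The cost is text only, with no extra enrolment. Because data are already being collected, the outcome named in step 1 must be the one used in the calculation, not one chosen now. If no record of it exists, the text should say so.

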### Analysis

The normality of the data will be verified with the Shapiro-Wilk test. Parametric data will expressed as mean and SD, using Student’s *t* test for independent samples to compare the groups and two paired samples to compare the times. For the analysis of repeated measures, analysis of variance with a post hoc Tukey test will be used. Nonparametric data will be expressed as median, maximum, and minimum values. The Mann-Whitney *U* test will be used to compare the groups, and for comparison of moments, the Wilcoxon test will be applied. In all tests, results will be judged to be statistically significant when α values are <0.05.

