#### Western Ontario and McMaster Universities Osteoarthritis Index

The Western Ontario and McMaster Universities Osteoarthritis Index (WOMAC) is a specific and reliable instrument for individuals with knee OA. This questionnaire consists of three domains: section A - pain (5 questions), section B - joint stiffness (2 questions), and section C - physical function (17 questions). The questions should be answered according to the subject’s perception of pain, joint stiffness, and level of physical function within the last 72 h. The WOMAC scores are presented on a Likert scale in which each question receives a score ranging from 0 to 100, distributed as follows: none = 0, light = 25, moderate = 50, severe = 75, and extreme = 100. The results will be determined from the sum of points of each question and divided by the number of domain questions. In this way, the final three scores will be obtained, one for each domain [19, 20].

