### Pain perception assessment

A dolorimeter (Palpeter®; Sunstar Suisse, Etoy, Switzerland), in the form of 1 kg, and a visual analogue scale (VAS) will be used. The dolorimeter consists of a plastic casing with a retractable, cylindrical aluminum ferrule 10 mm in diameter. The examiner should hold the plastic casing with the thumb and third finger by placing the index finger on the instrument orifice. Thus, the pressure exerted will be maintained for 3 seconds on each of the four previously defined anatomical points: (a) lateral joint interline, (b) medial joint interline, (c) medial condyle of the femur, and (d) the lateral condyle of the femur. Then, the volunteers should be classified for pain intensity according to VAS. This consists of a 10-cm line containing numbers ranging from 0 to 10, where 0 represents “no pain” and 10 represents “worst possible pain” [21].

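### A Shapiro-Wilk result on the trial's own data chooses each outcome's test and summary, so related outcomes can be analysed on different scales without a planned reason

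*Protocol article*

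**What the plan says.** The Analysis section of the protocol article opens with "The normality of the data will be verified with the Shapiro-Wilk test" and then splits into two routes.

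- **Route for data judged normal:** "Parametric data will expressed as mean and SD, using Student’s" t test between groups, with a paired version between times. The section adds: "For the analysis of repeated measures, analysis of variance with a post hoc Tukey test will be used".
- **Route for the rest:** "Nonparametric data will be expressed as median, maximum, and minimum values". On testing, the Mann-Whitney U "test will be used to compare the groups, and for comparison of moments, the Wilcoxon test will be applied".

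The threshold is common to both routes: "In all tests, results will be judged to be statistically significant when α values are <0.05". The section does not say whether normality is judged on pooled values, by arm and moment, on changes or on residuals.

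Several outcomes are bounded. Pain is rated on a "10-cm line containing numbers ranging from 0 to 10". Each WOMAC item is scored 0 to 100 in steps of 25 and averaged within its domain; the stiffness domain has two items. The sample is 15 per group (Sample size; Randomization and allocation).

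**The concern.** A preliminary test on the collected data selects the method, and the two methods answer different questions: a difference in means, or a comparison of ranks. At 15 per arm a normality test is weak evidence about shape and varies by chance from one outcome to the next. Sibling measures, such as the three WOMAC domains or the four pain points, could be tested and summarised differently although nobody planned that they should be. A borderline result could turn on the route taken.

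There is also a feedback for bounded scores. The article expects less pain and lower WOMAC scores in the aquatic arm. If that moves values onto the floor of the scale, the shape changes, and the effect under study can then alter the method used to estimate it.

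**Working it through.** **Inputs from the document.** 15 per arm; 0.05 for all tests; pain 0-10; WOMAC items in steps of 25.

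**Assumed, because the document gives no values.** Distribution shapes, means and SDs; M1-M3 correlation 0.6; Shapiro-Wilk at 5%; full reassessment at M3. The effect of 1.06 SD is what 15 per arm detects with 80% power in a two-sided 5% t test, reading the stated beta of 80% as power. The article states no effect size, so there is no planning figure to reproduce on this point.

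**1. Chance routing with exactly normal data.** Two arms at two moments give four cells. P(at least one rejects) = 1 - 0.95^4 = 0.185; simulation gave 18-19%. Counting 4 WHOQOL-BREF domains, 3 WOMAC domains, 4 pain points, TUG and sit-and-reach gives 13 outcomes, and 13 × 0.185 = 2.4. With one combined pain score there are 10 outcomes, and 10 × 0.185 = 1.9. So about two outcomes would have a rejecting cell by chance alone. The rate depends on the unit checked. For one moment it is 4.8% if the 30 values are pooled and 9.5% if either arm may fail.

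**2. Skewed or coarse data.** With lognormal data (log-SD 0.4), the four cells disagree in about 70% of outcomes. WOMAC stiffness can take only 9 values, since the sum of two items runs from 0 to 200 in steps of 25. For a score of that kind the cells disagree in about 42-60%.

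**3. Does the route matter?** Share of trials in which t and Mann-Whitney fall on opposite sides of 0.05, effect 1.06 SD:

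| Shape | Disagreement |
|---|---|
| Normal | 6.0% |
| Gamma, skew 1 | 7.4% |
| Lognormal, log-SD 0.5 | 10.0% |
| Exponential | 11.9% |

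Across all runs the range was roughly 4-12%, with one skewed-shift case at 14%.

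**4. Can the effect change the route?** Rejection rate in the aquatic-arm M3 cell, pain score rounded to whole numbers, SD 2:

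| Assumed mean | No effect | 1.06 SD |
|---|---|---|
| 2.5 | 22% | 98% |
| 4 | 13% | 46% |
| 5 | 13% | 18% |

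With an unrounded score and either arm allowed to fail, the rank route rises from 12% to 78% (mean 3), 8% to 32% (mean 4) and 8% to 11% (mean 5). If skewed data are pooled the rate falls instead: 44% to 21% (gamma) and 72% to 38% (lognormal, log-SD 0.5). A pure shift leaves by-arm normality unchanged.

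**5. Error rate of the two-stage rule.** Overall type I error was 0.045 to 0.059.

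**6. Power of the two-stage rule.** Gate against a fixed t test at the same moment, 1.06 SD, with a linear model that adds the M1 value in the last column:

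| Shape | Gate | Fixed t | Model with M1 |
|---|---|---|---|
| Normal | 79.6% | 80.1% | 93.2% |
| Lognormal (log-SD 0.4), shift on log scale | 77.3% | 77.1% | 90.1% |
| Lognormal, additive shift | 86.3% | 81.4% | 92.3% |
| 0-10 score, mean 2.5 | 72.6% | 73.6% | 87.1% |

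The normal row can be checked by hand. Adjusting for M1 divides the SD by 1/sqrt(1 - 0.6^2) = 1/0.8, so the effective effect is 1.06/0.8 = 1.325. With 15 per arm, 90% power needs 1.226 and 95% needs 1.364, so 1.325 lies between them. The gain comes from the covariate. Removing the gate alone changes power by at most about 1 point in three rows and would lose about 5 points in the additive lognormal row.

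**The case against.** The strongest reply is that the decision rule is itself prespecified, that it keeps its error rate, and that a condensed article may leave the unit of the normality check to a fuller document. All of that stands. The silence on the unit is not the finding, and the four-cell figures hold only if cells are what is checked. The phrase about the data need not mean raw scores either.

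A reader might infer four stronger points that the document and the calculations do not support.

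- **Inflated false positives.** After passing a by-arm check, the t test's own error can rise (0.069 for lognormal data, 0.106 for exponential), but the error of the whole rule stays at 0.045 to 0.059.
- **Lost power.** The gate matches a fixed t test or beats it. On skewed data Mann-Whitney can be the better test (89% against 81% for lognormal data with log-SD 0.5), so the rank route is not worthless.
- **Routing always driven by the effect.** This needs a bounded score near its floor, or pooled skewed data. TUG and sit-and-reach have no floor at zero that benefit would approach.
- **No comparison over time on the rank route.** The article names Wilcoxon for moments, and paired t tests on the other route. Only the ANOVA lacks a named rank counterpart.

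What the reply does not answer is that the scale on which each outcome is tested and reported remains open until the data are seen.

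**Conclusion.** The point holds as a minor one. The stated rule leaves the test and estimand of each outcome to a noisy preliminary test, so sibling outcomes can be reported on different scales by chance. If cells are checked separately, about 19% of outcomes have a rejecting cell with normal data, and about 70% have conflicting cells with moderate skew. The choice of test changes significance in roughly 4-12% of trials when there is an effect. Dependence of the route on the treatment effect is conditional: large at an assumed pain mean of 2.5, slight at a mean of 5. These sizes rest on assumed shapes and a correlation of 0.6. The harm is inconsistent estimands and reporting, not a distorted error rate or lost power.

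**What to change.** Drop Shapiro-Wilk as the selector. State now, for every outcome whatever its distribution:

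- **Main between-arm analysis:** the difference in means at M3 from a linear model with the M1 value as covariate, with a 95% CI and, if wanted, a p-value by permutation of arm labels.
- **Sensitivity analysis, labelled as such:** Mann-Whitney with a Hodges-Lehmann difference, or rank ANCOVA. On the four shapes in the power table, rank ANCOVA reached 90.3%, 90.7%, 95.3% and 86.4%.
- **Diagnostics:** residuals inspected descriptively, with no effect on the choice of method.
- **Summaries:** mean, SD, median and quartiles for all outcomes, in place of a summary that depends on the route.

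The cost is one paragraph, with no new data or participants. The Trial status section says data are still being collected, so the wording can be settled before analysis. The covariate also raises power, from about 80% to 93% on normal data at the assumed 1.06 SD and correlation 0.6, but that is a separate benefit. The downside is that a mean difference describes a strongly skewed or floor-bound score less naturally, and a rank test can have somewhat more power there. The sensitivity analysis and quartiles cover this.

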## Discussion

The objective of this clinical trial is to evaluate the effect of aquatic physical therapy in older people with knee OA. The study is guided by practice-based scientific evidence for the use of aquatic rehabilitation exercises for this condition.

Upon completion of data collection, it is expected that the WG volunteers will benefit from increased flexibility through the Wells test, improved functional capacity through the TUG test, reductions in scores on the WOMAC, and quality of life assessed by the WHOQOL-BREF. In the CG, no changes in the values of any variable analyzed are expected. It is believed that the desired results could be attributed to physical and physiological effects of immersion in heated water associated with the proposed exercise protocol. The data will be published after the study is completed.

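### Before-after tests within each arm have the same standing as the between-group tests, so the plan allows a treatment effect to be inferred from a change that is significant in the aquatic group and not in the control group

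*Protocol article*

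**What the plan says.** The Analysis section names two kinds of test in each branch. For data treated as parametric, Student's t test is used "for independent samples to compare the groups and two paired samples to compare the times". For the nonparametric branch, the Mann-Whitney U "test will be used to compare the groups, and for comparison of moments, the Wilcoxon test will be applied". A further sentence adds: "For the analysis of repeated measures, analysis of variance with a post hoc Tukey test will be used". The factors of that analysis of variance are not given. One threshold covers everything: "results will be judged to be statistically significant when α values are <0.05".

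The section does not say whether the groups are compared on post-intervention values, on change, or at each moment. Nor does it say which of these tests carries the conclusion about efficacy.

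The Discussion gives the anticipated result arm by arm. For the intervention arm, "it is expected that the WG volunteers will benefit from increased flexibility through the Wells test", followed by similar expectations for the other measures. For the control arm, "In the CG, no changes in the values of any variable analyzed are expected". It then attributes the hoped-for results to warm-water immersion combined with the exercise protocol.

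**The concern.** A significant change in one arm and a non-significant change in the other does not show that the arms differ. The two p-values answer two separate questions, and neither is the randomised comparison. With 15 people in CG, a non-significant change is also weak evidence of no change.

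The within-arm tests matter because both arms can plausibly move without any treatment effect. Timed Up and Go and sit-and-reach take the best of three attempts and are repeated, so practice may help both arms. Participants are referred patients, so regression to the mean and natural course may also act. A paired test in WG absorbs all of this into the apparent effect. The plan places a valid and an invalid route to an efficacy claim side by side, ranks neither, and describes its expected result in the terms of the invalid one.

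**Working it through.** **1. The plan's own figure.** The Sample size section gives 15 per group, with alpha 5% and a stated beta of 80%, read here as power 80%. No outcome, effect size, SD or test is given, so 15 cannot be reproduced. Solving backwards (two-sided 0.05, power 80%, n = 15), an independent t test needs a standardised difference of 1.06 and a paired t test a standardised change of 0.78. Either test could lie behind the figure, so the sample size does not reveal which test is meant to decide.

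**2. What the named tests cover.** The between-group tests compare arms. The paired and Wilcoxon tests compare times within an arm. In the nonparametric branch nothing links the two. In the parametric branch the analysis of variance might contain a group-by-time term, but this is not stated. Tukey's procedure does not settle it: with two arms it adds nothing to a group comparison, and it has work to do only across three or more moments or group-by-moment cells.

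**3. Size of the problem if the within-arm pattern were read as the effect.**

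Inputs: n = 15 per arm (protocol); alpha 0.05 (protocol), two-sided (assumed); the same true change in both arms, so no treatment effect (assumed); standardised change dz = mean change / SD of change, varied from 0 to 1.0 (assumed, as the protocol gives no figure).

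For a paired t test, the noncentrality is dz × √15 and the critical value is t(14, 0.975) = 2.145. The arms are independent, so

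P(pattern) = P(WG significantly improved) × P(CG not significant).

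| dz | dz × √15 | WG significantly improved | CG not significant | Product |
|---|---|---|---|---|
| 0 | 0 | 0.025 | 0.950 | 2.4% |
| 0.2 | 0.77 | 0.108 | 0.888 | 9.6% |
| 0.3 | 1.16 | 0.190 | 0.809 | 15.4% |
| 0.4 | 1.55 | 0.303 | 0.697 | 21.1% |
| 0.54 | 2.09 | 0.495 | 0.505 | 25.0% (maximum) |
| 0.7 | 2.71 | 0.713 | 0.287 | 20.5% |
| 0.8 | 3.10 | 0.821 | 0.179 | 14.7% |
| 1.0 | 3.87 | 0.949 | 0.051 | 4.8% |

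A simulation of 100,000 trials gave 15.4%, 25.1% and 14.7% at dz = 0.3, 0.54 and 0.8.

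In baseline SD units, dz = shift / √(2(1 − r)), where r is the baseline-to-follow-up correlation. A shift of 0.3 SD with r = 0.5 gives dz = 0.30; a shift of 0.6 SD with r = 0.7 gives 0.6 / 0.775 = 0.77.

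**4. The between-arm alternatives under the same common change.** An independent t test on change scores rejected in 4.9% to 5.1% of simulated trials, two-sided, so about 2.5% in WG's favour. An independent t test on post values, with a common shift of 0.5 SD and r = 0.5 or 0.7, rejected in 4.7% and 5.1%. Both hold the nominal level.

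**The case against.** The strongest reply is that the plan does compare the randomised groups. Both branches name a between-group test, and name it before the within-arm one. Compared on post-intervention values, randomised groups are protected against a common change, as step 4 shows. The Discussion sentence on CG is an expectation and not a decision rule. An article also commonly leaves model terms to a fuller document, so the unstated ANOVA factors are not a defect in themselves.

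All of this stands, and it limits the point. A reader might infer that the effect will be read from the within-arm tests, that the control group is not used for the main inference, or that success is defined as WG changing while CG does not. The protocol does not support any of these: it plans group comparisons and states no success criterion. Nor does it support multiplying the percentages by the number of outcomes to predict a count of false findings, because that would need every outcome to share a common change of this size. The 0.3-0.8 range is also the least favourable part of the scale; the risk is lower at 0.2 and at 1.0.

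The reply does not remove what the article itself states: within-arm significance tests at 0.05, unranked against the group tests, beside an expected result worded as within-arm change in one group and none in the other.

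**Conclusion.** The concern holds in a conditional form. The plan does not commit to the within-arm reading, but leaves it open and describes its expected result in those terms. If that reading were used, a change common to both arms would yield a false WG-only result in about 15-25% of outcomes at a standardised change of 0.3-0.8 (about 10% at 0.2, 5% at 1.0, 2.4% at 0), against about 2.5% for a between-arm test. These figures rest on 15 per arm, two-sided 0.05, approximately normal changes, equal true change in both arms, and an assumed size of that change. If conclusions rest on the planned between-group tests of post values, there is no inflation.

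**What to change.** Amend the Analysis section before the data are analysed:

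- Make the between-arm contrast at M3 the only basis for efficacy conclusions, with its 95% CI. Use ANCOVA adjusted for the M1 value, or the group-by-time contrast of a mixed model for outcomes measured at more than two moments, in place of the unspecified ANOVA with Tukey.
- Name the between-arm counterpart for non-normal data, for example rank ANCOVA or Mann-Whitney on change.
- Report within-arm changes descriptively, without p-values.
- State that a non-significant change in CG will not be used as evidence of effect.

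Adjustment for M1 should also help precision. At an assumed true difference of 1.06 SD with 15 per arm, a test on post values has 80% power. ANCOVA has about 84%, 90% and 97% at r = 0.3, 0.5 and 0.7. A change-score test has about 66%, 80% and 95%, so ANCOVA is the safer default where r may be low.

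The cost is a change of wording, slightly more analysis work and the loss of within-arm significance claims. It uses the measurements already planned.

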**Methods/design:**

This is a parallel, two-arm, open, randomized controlled clinical trial with older people with knee OA. Volunteers will be allocated to an aquatic intervention group (WG), subjected to the intervention, or to a control group, not be subjected to any kind of intervention. Data collection pre- and postintervention will be composed of the evaluation of the perception of pain by visual analogue scale with application of nociceptive stimuli in four anatomical points of the knee, functional fitness tests, and application of the World Health Organization Quality of Life Scale abbreviated version and Western Ontario and McMaster Universities Osteoarthritis Index. The program will last 12 weeks, consisting of aerobic and functional exercises in the form of circuit training.

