Thus, the study will be divided into four moments: M_0_ (recruitment and screening), M_1_ to test and evaluative measures, and M_2_ and M_3_ for evaluation of the flexibility and reevaluation of tests and measurements (Fig. 1).

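### The tests named for comparing groups carry no baseline adjustment, and the one analysis that uses baseline states no group-by-time contrast; this costs precision, not validity

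*Protocol article*

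**What the plan says.** The Analysis section opens with a gate: "The normality of the data will be verified with the Shapiro-Wilk test". The route then depends on the result.

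- Parametric data: Student's t "test for independent samples to compare the groups and two paired samples to compare the times".
- Repeated measures: "For the analysis of repeated measures, analysis of variance with a post hoc Tukey test will be used".
- Nonparametric data: the Mann-Whitney U "test will be used to compare the groups, and for comparison of moments, the Wilcoxon test will be applied".

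So two tests are assigned to the comparison of groups, and neither is given a baseline covariate or said to be run on change scores. The paired t and Wilcoxon tests are assigned to the comparison of times or moments. The ANOVA is given no group factor, no interaction term and no place in the decision.

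Baseline values exist. The abstract (Methods/design) says "Data collection pre- and postintervention will be composed of the evaluation of the perception of pain by visual analogue scale" and adds the functional tests, WHOQOL-BREF and WOMAC. The section on intervention and follow-up periods schedules "M_1_ to test and evaluative measures, and M_2_ and M_3_ for evaluation of the flexibility and reevaluation of tests and measurements". That sentence is slightly ambiguous on whether flexibility is measured at M1, but the abstract places the functional fitness tests before as well as after the intervention.

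**The concern.** With 15 per arm, the trial can detect only large differences, so it matters how well the between-group comparison uses the data. The M1 value of the same outcome is usually an informative covariate, and it is already in the schedule. The tests named for comparing groups are not stated to use it. The tests that clearly use it (paired t, Wilcoxon) look at change within groups and do not test the effect of the intervention.

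Allocation is by simple draw with no stratification described. The difference between arms in the baseline mean therefore has a standard deviation of √(2/15) = 0.37 SD on any one outcome. An unadjusted comparison of follow-up values carries r times the observed imbalance into the estimate, where r is the correlation between baseline and follow-up.

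The normality gate adds to this. It can switch the reported quantity from a mean difference to a rank comparison, outcome by outcome, and the switch moves an outcome onto the route where no between-group test is stated to use baseline.

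**Working it through.** **Inputs from the protocol article.** 15 per group (Randomization and allocation; Sample size); alpha 5% (Sample size; Analysis); "beta of 80%" in the Sample size section, read here as 80% power.

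**Assumptions.** Two-sided testing; normal outcomes with equal SD at M1 and M3; correlation r = 0.3, 0.5 or 0.7. The document gives neither r nor an effect size.

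**Step 1: the plan's own figure.** The Sample size section gives no effect size, SD or test, so 15 per group can only be solved backwards, using the noncentral t with 28 degrees of freedom:

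- two-sided, 80% power: d = 1.06
- one-sided, 80% power: d = 0.93
- two-sided, 20% power (beta of 80% taken literally): d = 0.42

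The figure can be neither confirmed nor refuted. The first reading is used below.

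**Step 2: formulas.** The noncentrality is d × √(15/2), divided by the square root of a variance factor:

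- unadjusted t test: factor 1, df 28
- ANCOVA on M1: factor 1 − r², df 27
- change score, which equals the group-by-time interaction over two occasions: factor 2(1 − r), df 28

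**Step 3: one case in full, d = 0.7 and r = 0.5.**

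- Unadjusted: 0.7 × √7.5 = 1.917; critical t 2.048; power 46%.
- ANCOVA: 1.917 / √0.75 = 2.214; critical t 2.052; power 57%.
- Change score: 1.917 / √1 = 1.917; power 46%.

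**Step 4: results.** The unadjusted t test detects 1.06 SD with 80% power and has 46% power at 0.7 SD, whatever r is.

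| | r = 0.3 | r = 0.5 | r = 0.7 |
|---|---|---|---|
| Variance left by ANCOVA, 1 − r² | 0.91 | 0.75 | 0.51 |
| Cut in variance | 9% | 25% | 49% |
| Equivalent n per arm, 15/(1 − r²) | 16.5 | 20 | 29.4 |
| Detectable difference, ANCOVA | 1.01 SD | 0.92 SD | 0.76 SD |
| Power at 0.7 SD, ANCOVA | 49% | 57% | 73.5% |
| Power at 0.7 SD, change score | 35% | 46% | 67% |
| Power at 1.06 SD, ANCOVA | 83.5% | 89.8% | 97.5% |
| Power at 1.06 SD, change score | 66% | 80% | 95% |

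**Step 5: simulation check** (10,000 trials per setting). At 1.06 SD, ANCOVA reached 82% / 89% / 97%. This is slightly below the formula, which ignores the small cost of chance imbalance. Mann-Whitney reached 76-77%. A repeated-measures ANOVA read on its group main effect reached only 41% / 38% / 33%. With no true effect, the unadjusted t and Mann-Whitney tests rejected in about 4-5% of trials.

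**The case against.** The strongest objection is the ANOVA sentence. It sits in the same paragraph, and it uses M1. If group and time are both factors, the interaction is a between-group test of change. A reader who sees only the t and Mann-Whitney sentences might infer that the trial discards its baseline data. The document does not support that for parametric outcomes, and the full protocol or an analysis plan may specify the model.

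That stands, but it does not settle the point. The article assigns the comparison of groups to the t and Mann-Whitney tests, and says nothing of an interaction or of which analysis decides. Even on the generous reading, the two-occasion interaction is a change-score test: less powerful than ANCOVA at each r shown, and worse than ignoring baseline below r = 0.5. The nonparametric route has no counterpart to the ANOVA.

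Four more objections limit the claim:

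- The article does not say whether the t and Mann-Whitney tests are run on M3 values or on changes. The unadjusted figures assume M3 values; if changes were meant, the change-score rows apply.
- The gain depends on r. At r = 0.3 it is small, and at r = 0 ANCOVA loses about 0.1 percentage point of power. That baseline adjustment would bring a large gain is therefore not established.
- A reader might infer that chance imbalance biases the result. It does not: randomization keeps the unadjusted tests valid, and their standard error already allows for such imbalance.
- A reader might infer that the normality test must miss most skewed data. For three assumed skewed distributions, its power is 21% to 37% if each arm of 15 is tested, but 44% to 75% if all 30 values are pooled. The article does not say which is meant.

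**Conclusion.** The point holds in a limited form. The two tests named for comparing groups are stated without baseline adjustment, the analysis that does use M1 specifies no group-by-time contrast, and the Mann-Whitney/Wilcoxon route has no between-group test stated to use baseline. The consequence is avoidable imprecision, ranging from slight at r = 0.3 to the equivalent of nearly doubling the sample at r = 0.7. These sizes rest on the assumed r, on two-sided testing, on reading the sample size statement as 80% power, and on group tests applied to follow-up values. The plan remains valid on type I error. The change is worth making because it needs no further participants or visits.

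**What to change.** While data are still being collected, as the Trial status section says, state one deciding between-group comparison for each outcome:

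- an ANCOVA of the M3 value on group and the M1 value of the same outcome, or a baseline-adjusted mixed model that also includes M2 where the outcome is measured then;
- the adjusted mean difference with its 95% CI, reported whatever the Shapiro-Wilk result;
- a rank-based ANCOVA or permutation test as a sensitivity analysis where residuals are clearly skewed;
- the within-group paired tests kept as description only.

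If the repeated-measures ANOVA stays, state its factors and its group-by-time contrast, and say that it is supportive. The M1 measurements are already in the schedule, so the cost is one degree of freedom, some analysis wording and a few lines of code.
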